## Abstract

**Background:**

Two types of methods are used to assess learning curves: outcome assessment and process assessment. Outcome measures are usually dichotomous rare events like complication rates and survival or require an extensive follow-up and are therefore often inadequate to monitor individual learning curves. Time-action analysis (TAA) is a tool to objectively determine the level of efficiency of individual steps of a surgical procedure.

**Methods/Design:**

We are currently using TAA to determine the number of cases needed for surgeons to reach proficiency with a new innovative hip implant prior to initiating a multicentre RCT. By analysing the unedited video recordings of the first 20 procedures of each surgeon the number and duration of the actions needed for a surgeon to achieve his goal and the efficiency of these actions is measured. We constructed a taxonomy or list of actions which together describe the complete surgical procedure. In the taxonomy we categorised the procedure in 5 different Goal Oriented Phases (GOP):

1. the incision phase

2. the femoral phase

3. the acetabulum phase

4. the stem phase

5. the closure pase

Each GOP was subdivided in Goal Oriented Actions (GOA) and each GOA is subdivided in Separate Actions (SA) thereby defining all the necessary actions to complete the procedure. We grouped the SAs into GOAs since it would not be feasible to measure each SA. Using the video recordings, the duration of each GOA was recorded as well as the amount of delay. Delay consists of repetitions, waiting and additional actions. The nett GOA time is the total GOA time – delay and is a representation of the level of difficulty of each procedure. Efficiency is the percentage of nett GOA time during each procedure.

**Discussion:**

This allows the construction of individual learning curves, assessment of the final skill level for each surgeon and comparison of different surgeons prior to participation in an RCT. We believe an objective and comparable assessment of skill level by process assessment can improve the value of a surgical RCT in situations where a learning curve is expected.

## Background

### Introducing new techniques

Surgical expertise is a relatively under-explored item in surgical trials. Often, results of surgical trials are reported without information on the participating surgeons expertise in a new treatment option [1]. Critics used this argument against the utilization of randomized controlled trials (RCT) in surgery [2]. When surgeons plan an RCT comparing a well established implant with a relatively low morbidity to a new, potential superior, implant; a surgeon has to weigh the additional benefits to possible morbidity the new implant may give. Using innovative implants possibly exposes a patient to risks due to the surgeon's inexperience introducing the new surgical technique, perhaps leading to an increase of complications or decreasing the functional result.

Through clinical trials, functional result as well as complications can be evaluated. Clinical trials however evaluate the outcome of the procedure as a whole and are therefore inadequate to determine which specific pitfalls are inherent in the operation itself. By determining these pitfalls within the operation, the surgeon can possibly anticipate them and thereby avoid them.

Moreover, random variation of surgical outcome is influenced both by number of cases included and the frequency with which the outcome occurs. In circumstances where the expected outcome is rare, outcome indicators will have only limited power to detect real differences in quality [3]. A surgical technique with a low complication rate requires a high amount of surgical procedures with a long term follow-up for these complications to occur. This is particularly the case when evaluating the outcome of innovative prosthetic implants [4-6]. However, when introducing a new innovative implant it is important to identify pitfalls and difficulties at an early stage, preferably during the first few cases, thereby minimising risk for subsequent patients in a planned RCT evaluating the new implant. Identifying pitfalls of a surgical technique during a learning curve therefore ideally requires a system which:

- is capable of analysing individual steps of a surgical procedure

- requires a small amount of procedures (small number of cases)

- does not require a long follow-up and provides immediate feedback

- is able to detect these pitfalls

- is reproducible

This calls for process instead of outcome measurement. Outcome measures are most relevant for the broader perspective since they reflect the inter-play of a wide variety of factors. With a narrow perspective, on individual learning curves, process measurements become relatively more useful. Process measurements are often only considered useful if they are assumed to correlate with clinical outcome [3]. However, considering that errors within a process can have a synergistic effect it is important to focus on all errors not just those directly associated with a poor outcome [7]. Errors can be categorised by active and latent errors. Active errors have an immediate effect on outcome, while latent errors are hidden within the system, until their synergistic effects will accumulate with resulting adverse events [8,9].

Process measurement can be performed by two methods: Implicit and explicit. Implicit methods require expert judgement, without predefined criteria. Explicit methods assess quality of care against predefined criteria or algorithms, thereby providing standardised comparative and reproducible data [7]. In this study we aim to compare several surgeons and several procedures, necessitating an explicit reproducible measurement method. A previous pilot study performed at the Orthopaedic Research Centre Amsterdam by Veth and De Beer has shown an inter-observer reliability (expressed as IntraClass Correlation Coefficient) of 0.78 to 0.91 for anterolateral minimally invasive total hip arthroplasty, demonstrating it to be a reproducible tool to evaluate a perioperative process objectively.

### Time-action analysis

Time-action analysis (TAA) is a tool to objectively determine the level of efficiency of individual steps of a surgical procedure [10-13]. By analysing unedited video recordings of a surgical procedure the number and duration of the actions needed for a surgeon to achieve his goal and the efficiency of these actions is measured. In the past TAA has successfully been used to evaluate laparoscopic procedures and total shoulder arthroplasty procedures [10-13]. Utilizing TAA a surgeon is able to recognise and anticipate specific pitfalls. It can also be used as a tool to evaluate the improvement of efficiency and the decrease of errors in time as a representation of the learning curve. By comparing the surgical technique of experienced surgeons with inexperienced surgeons, difficult steps which need further emphasis during the learning curve can be identified and errors possibly avoided. Furthermore it can provide feedback to manufacturers of surgical materials, consequently they can determine how improvements in surgical material can increase efficiency. Even though conducting a fully efficient procedure does not ensure good clinical outcome, improvements in surgical techniques is the most important way in which a surgeon can alter the outcome.

### Femoral neck preserving hip arthroplasty

The Biodynamic cementless total hip prosthesis, introduced by Pipino in 1979, was designed with the aim to preserve maximum amount of bone stock for future revisions, to achieve physiological compression, tension and torsion forces and to minimise damage to vascular structures in the proximal femoral region [14,15]. The Biodynamic stem was replaced by the modified CFP prosthesis in 1996. The CFP prosthesis is made of titanium alloy with a hydroxyapatite porous coating, with longitudinal ribs to promote osseointegration. A seven year follow-up study of 353 CFP stem showed 99% good intergration, with only 2 cases of radiographically proven aseptic loosening [16]. It has a built in anatomic anteversion and 117° and 126° CCD angles to closely resemble physiological anatomy. Clinical follow-up showed good functional recovery and DEXA analysis of 10 patients showed minimal periprosthetic bone loss [14,16,17,17]. The CFP stem is combined with a Trabeculae Oriented Pattern (TOP) cementless hemispheric cup. The TOP cup has a biequatorial dissociation with a medialcaudal recess to allow a wider range of motion and a cranial rim reaching over 180° to reduce the risk of dislocation [14]. A clinical follow-up study of 301 TOP cups showed no detachement, migration, or osteolysis after 7 years [16].

Currently the CFP stem has not been compared with conventional straight stems in an RCT, therefore additional benefits remain to be determined. Implantation of the CFP stem requires a major alteration of operating technique compared to conventional straight cementless stems and require specially designed instruments. Therefore a substantial learning curve is to be expected potentially compromising the validity of an RCT due to differential expertise based bias. Determining the minimum number of cases required before participating in an RCT is often arbitrary and for many complex procedures the learning curve has not reached a plateau after reaching the required number of procedures [2]. Another potential for differential expertise bias is the influence of the number of years of clinical experience of participating surgeons [2].

We aimed to evaluate the learning curve of experienced hip surgeons who will be participating in a future RCT evaluating the CFP stem. We hypothesized that using TAA could result in a clear understanding of a surgeon's learning curve and finally surgical expertise before embarking in an RCT comparing the CFP stem with a straight stem in total hip arthroplasty. By determining a surgeon's learning curve prior to initiating an RCT we aim to determine and possibly reduce the influence of differential expertise bias.

### Main objective/research question

What is the number of cases needed for surgeons with different levels of experience to reach proficiency with the CFP stem arthroplasty?

### Secondary objective/research question

Do surgeons with much experience learn a new technique more rapidly than a surgeon with less experience?

### Hypothesis

We hypothesize that after 10–15 cases, surgeons will reach a plateau of the level of efficiency. We expect to register a significant decrease of errors during this period. Furthermore we expect no correlation to exist between change of functional outcome or complication rate and case number.

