#### Secondary outcome parameters

##### Functional outome

As part of current clinical protocol, functional outcome will be measured using the Dutch version of the Hip disability and Osteoarthritis Outcome Score (HOOS), validated by De Groot et al [18]. Functional score will be recorded pre-operatively and at 6 weeks, 3 months and one year follow-up, as part of standard follow-up protocol [18]. Follow-up protocol is not affected by this study.

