### Sample size

Since there is currently no data on the learning curve of the CFP stem, sample size is estimated by reviewing the learning curve of other implants or techniques in current literature. Previous literature on learning curves in total hip and total knee arthroplasty determine the learning curve on the amount of complications, clinical outcome, implant position or mean operative time [6,19].

Archibeck et al. analysed the first experience of 159 surgeons with the 2-incision minimally invasive THA. He found a significant reduction in the mean operative time in the first ten cases. The amount of complications did not show any reduction as a function of the case number [19].

Flamme et al. studied the learning curve in total hip arthroplasty of three surgeons with different levels of experience operating on a total of 168 patients. They found no association between functional outcome as determined by the Merle d'Aubigné score and case number. However considering intraoperative complication rate, all three surgeons ended their learning curve after a maximum of 20 cases [6]. Based on these studies, we estimate the efficiency to reach a plateau between 10 and 20 cases. Therefore the first 20 cases of each surgeon will be analysed.

A learning curve can however differ between individual surgeons. It is therefore important to study multiple surgeons with different levels of experience and to define a stopping rule. The stopping rule defines whether the estimated number of 20 cases is sufficient to study an individuals learning curve and terminate the task analysis or whether additional cases are needed. The criterion for terminating the task analysis was previously determined through the probability of failure (P) multiplied by the cost of failure (C) to an acceptable level – the P × C rule [20]. The role of the P × C rule is to save the analyst time in analysing tasks where the error variance would be inconsequential and to guide more exploration where the error variance would be intolerable [20]. The cost of failure is inherent to the clinical consequence of a peri-operative complication which requires clinical interpretation. We defined three major peri-operative complications during total hip arthroplasty which determined C:

1. massive bleeding

2. fracture (femoral or acetabular)

3. evident neurological damage

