This resulted in the following definition of the stopping rule: if a surgeon encounters a major complication (C) within the last five consecutive surgical procedures (P), the stopping rule is considered unacceptable and an additional five surgical procedures have to be analysed.

To facilitate comparison of different levels of expertise we suggest one surgeon less than five years board certification, two surgeons 5 to 15 years and 1 surgeons more than 15 years board certification. This justifies our total sample of 4 surgeons each performing 20 cases, resulting in a total of between 80 surgical interventions to be analysed.

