#### Functional outcome

To measure postoperative functional outcome the validated Dutch version of the Hip disability and Osteoarthritis Outcome Score (HOOS) taken pre-operative, within one week before the operation and postoperative at 6 weeks and one year follow-up [18]. Questionnaires will be collected by local surgical staff and send to the trial committee.

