##### Data analysis

A regression analysis will be performed to reveal any significant increase of efficiency or decrease of the errors rate as a function of the case number.

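### The margin-free hypothesis of no correlation between function or complications and case number is one that a non-significant result from 80 cases could not support

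*Protocol article*

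**What the plan says.** The Hypothesis section of the protocol article expects a plateau in efficiency after 10 to 15 cases and a fall in errors, and then adds: "we expect no correlation to exist between change of functional outcome or complication rate and case number". No margin for a negligible correlation is given.

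The number of cases has another basis. Sample size draws on two earlier learning-curve studies and concludes: "Based on these studies, we estimate the efficiency to reach a plateau between 10 and 20 cases". It then states: "This justifies our total sample of 4 surgeons each performing 20 cases, resulting in a total of between 80 surgical interventions to be analysed". No event rate, standard deviation, effect size or power for function or complications enters. Data analysis names regression on case number for efficiency and error rate only.

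In the Background (Introducing new techniques), the article argues for process measures on the ground that, where the expected outcome is rare, "outcome indicators will have only limited power to detect real differences in quality".

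The HOOS schedule appears twice. Secondary outcome parameters says: "Functional score will be recorded pre-operatively and at 6 weeks, 3 months and one year follow-up". Outcome measurements lists a pre-operative score and then "postoperative at 6 weeks and one year follow-up", with no 3-month visit.

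**The concern.** An absence of association cannot be established by failing to find one, unless the study is precise enough to exclude associations that would matter. Here nothing says which associations would matter, and the sample was chosen for a different outcome. If complications are few, a non-significant relation with case number is the likely result even when a real learning effect exists, so it carries little information.

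This study is meant to inform surgeons' readiness before a randomised trial. If the expectation were later reported as borne out, readers could take it as evidence that early patients bear no extra risk, and the data would not support that.

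Two further points touch the same sentence. For intraoperative complications, the expectation sits uneasily with part of the article's own evidence and with its stopping rule. And the change in function that it refers to is not tied to a visit, while the two visit lists disagree.

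**Working it through.** **Inputs from the article.** 4 surgeons and 20 cases each (Sample size). 4 × 20 = 80, which reproduces the stated total. There is no power calculation to reproduce.

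**Assumptions.** Two-sided 5% level, complete data, no clustering by surgeon. Complication rates are illustrative. The split into first 10 and last 10 cases per surgeon (4 × 10 = 40 v 40) and the use of Fisher's exact test are also choices made here, because the article names no analysis for complications.

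**Complications.** Power is the sum, over all pairs of event counts (a, b) with Fisher p ≤ 0.05, of Bin(a; 40, p1) × Bin(b; 40, p2).

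| First 10 v last 10 | Expected events, 40 × (p1 + p2) | Power |
|---|---|---|
| 6% v 2% | 3.2 | 1.5% |
| 10% v 2.5% | 5 | 9% |
| 10% v 5% | 6 | 4% |
| 15% v 5% | 8 | 18% |
| 20% v 10% | 12 | 16% |
| 20% v 5% | 10 | 41% |

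With no event in one half, the smallest significant split is 6 v 0 (p = 0.026); 5 v 0 gives p = 0.055. At an overall rate of 3% to 5%, 80 cases yield 0.03 × 80 = 2.4 to 0.05 × 80 = 4 expected events. With 4 events, significance is out of reach even if all fall in the first half.

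The result does not hinge on splitting the series or on Fisher's test being conservative. A simulated trend test over cases 1 to 20 gives 8% power for a fall from 10% to 5% (about 6 events) and 25% for a fall from 20% to 5% (about 9 events).

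**Function.** The 95% interval around an observed r = 0 is ±tanh(1.96/√(n − 3)).

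- n = 80: 1.96/√77 = 0.223, so ±0.22.
- n = 20: 1.96/√17 = 0.475, so ±0.44.

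Power to detect r = 0.3, by Fisher's z with atanh(0.3) = 0.3095:

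- n = 80: 0.3095 × √77 = 2.716; Φ(2.716 − 1.96) = 78%.
- n = 20: 0.3095 × √17 = 1.276; about 25%.

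The per-surgeon figure matters because Participating centres says that each surgeon's learning is analysed.

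Power to show equivalence to zero, by two one-sided 5% tests with true r = 0 and n = 80, is 2Φ(atanh(m) × √77 − 1.645) − 1. For assumed margins m of 0.10, 0.20 and 0.30 it is 0%, 11% and 72%.

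**Cited evidence, side by side (Sample size).**

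- The 159-surgeon study of a two-incision technique found no fall in complications with case number. This agrees with the hypothesis.
- The three-surgeon study of 168 patients found no link between functional score and case number. This agrees too.
- The same three-surgeon study reports that, "considering intraoperative complication rate, all three surgeons ended their learning curve after a maximum of 20 cases". This points the other way.

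The stopping rule in the same section requires five more cases to be analysed when a major complication occurs within the last five. It thus treats a late complication as informative about whether 20 cases are enough.

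**HOOS visits.** Both lists contain pre-operative, 6 weeks and one year. Only Secondary outcome parameters contains 3 months. Neither section says which visit defines the change.

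**The case against.** The article words this as an expectation about secondary outcomes in an observational study. It nowhere says that a non-significant result will be taken as proof, and its stated limits on rare outcomes are the very reason for choosing process measures. Margins and interval reporting may stand in an analysis plan that is not shown. The complication rates, the split and the test are assumptions, and at 20% v 5% power rises to 41%.

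Much of this stands, and it limits the point in three ways.

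- A reader might infer that the article plans to report the learning phase as free of cost to patients. The document does not say so; this is a risk of the wording.
- A reader might infer that 80 cases can show nothing about function. That goes too far: pooled power is 78% at r = 0.3, and equivalence power is 72% at an assumed margin of 0.30.
- A reader might infer that the hypothesis contradicts the cited evidence. It does not as a whole: two of the three relevant results support it, and only one study's intraoperative complications disagree. The article's own complication outcome also includes postoperative events, so the endpoints are not identical.

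What the objection does not remove is that the sentence stands under Hypothesis, without a margin, for outcomes that did not determine the sample size. Leaving details to an analysis plan does not repair a hypothesis that non-significance would satisfy by default.

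**Conclusion.** The point holds in limited form. At the low complication rates assumed (6% v 2% up to 15% v 5%), power is about 1.5% to 18%, so a non-significant result could not support the hypothesis for complications. For function, a null result would leave correlations up to about ±0.22 pooled or ±0.44 per surgeon open. Both figures assume complete data and independent cases.

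For intraoperative complications only, the hypothesis is in tension with one of the two cited studies and with the stopping rule. That is a tension to explain, not a contradiction of the evidence overall.

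The HOOS discrepancy is real but separate and smaller. It concerns one visit, three time points are common to both lists, and the primary outcomes are unaffected.

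**What to change.** Replace the hypothesis of no correlation with estimation: report the slope of HOOS change on case number, and the complication rate by block of cases, each with a 95% interval. State that non-significance will not be read as no association, and that complications are descriptive. Add a sentence acknowledging that the cited evidence on complications is mixed and explaining how the expectation fits with the stopping rule.

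Separately, reconcile the two HOOS schedules and name one visit listed in both as the basis for the change in function.

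The cost is wording and a weaker claim. No further cases or measurements are needed.

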### Study design

We propose a prospective observational study of 4 surgeons across 2 centres using Time-action analysis to analyse the level of efficiency of the surgical technique of surgeons with different levels of experience with the CFP stem and with varying clinical experience.

## Methods

### Outcome

#### Primary outcome parameters

• Nett Goal Oriented Action Time = time spend on Goal Oriented Actions (GOAs) – delay

• Delay = time spend on repetitions, additional actions and waiting

• Efficiency = percentage of nett Goal Oriented Action Time during each procedure

• Level of difficulty = Nett Goal Oriented Action Time of a specific GOA + time spend on repeating that GOA during subsequent GOAs

